### Safety aspects and adverse advents

Both surgical techniques are well established procedures and no specific side effects are expected in addition to the known complications of liver resections. Furthermore, the responsible surgeon can change the procedure at any given time point during the operation.

All precautions will be used to minimize the potential risks of bone marrow puncture which are bleeding, hematoma and infection. Since the central venous catheter for blood sampling is routinely placed in the operating theatre, no potential adverse effects of the blood sampling are expected.

Adverse events will be recorded during the hospital stay and the follow up.

### Ethics and informed consent

The final protocol was approved by the ethics committee of the University of Heidelberg. Written informed consent is obtained from each patient in oral and written form before inclusion in the study. The investigator will not undertake any measures specifically required only for the clinical trial until valid consent has been obtained. This must be done in accordance with the national and local regulatory requirements.

Patients are informed about the strict confidentiality of their personal data within this trial, but their medical records may be reviewed for trial purposes by authorized individuals other than their treating physician.

Patients will be informed about the additional specific risk of a bone marrow aspiration, which is voluntarily and will not lead to exclusion from the study in case of refusal.

It will be emphasized that the participation is voluntary and that the patient is allowed to refuse further participation in the protocol whenever he/she wants. This will not prejudice the patient's subsequent care.

The informed consent procedure is in accordance with the ICH guidelines on Good Clinical Practice.

### Follow up

The patients will undergo routine follow-up (physical examination of the patients, tumor markers (CEA), abdominal ultrasound and/or CT/MRI, chest X-ray, colonoscopy) at least once a year. Disease free survival and overall survival will be recorded; at each time point a follow-up evaluation form will be completed.

As the prognostic impact of disseminated tumor cells is still unclear, the clinical management and postoperative treatment of the patients will not be influenced by the results of this study. Decisions about further adjuvant treatment (e.g. chemotherapy) of the patients are left to the discretion of the treating oncologist.

### Data management and quality assurance

This trial is coordinated by the Department of Surgery at the University of Heidelberg. The data regarding tumor cell detection in blood and bone marrow of all patients will be entered in a password-protected database at the Department of Surgery, University of Heidelberg. The clinical data of all included patients will be centrally collected in a database at the Department of Surgery, University of Heidelberg. To transfer the data to Heidelberg, the evaluation forms will be sent from the participating centers via overnight service. The clinical and laboratory data will be merged in the password-protected database at the Department of Surgery, University of Heidelberg, Germany.

All samples and clinical data will be tracked by means of a unique research tracking number that will not be related to any patient identifying information. The link between research tracking numbers and patient identifiers will be kept in a limited access database on a computer with password protection. Routine data quality reports will be generated to assess missing data and inconsistencies. Accrual rates and accuracy of evaluations and follow-up will be monitored periodically throughout the study period and potential problems will be brought to the attention of the study team for discussion and action. Random-sample data quality and protocol compliance audits will be conducted by the study team.

Only surgeons who performed 25 or more successful liver resections are allowed to recruit patients for this study. The records of the operations will be reviewed centrally in order to identify protocol violations.

### Analysis

We evaluate the influence of two different liver resection techniques on the incidence of intraoperative hematogenous tumor cell dissemination in patients with colorectal liver metastases. Patients with circulating tumor cells present in the bloodstream at baseline (before operation) will be excluded from the primary analysis, hence the primary endpoint is the presence of disseminated tumor cells after liver resection. Details of the timing of the different blood samples drawn from each patient are provided.

The analyses will be performed as intention to treat analyses.

An interim analysis regarding the incidence of intraoperative tumor cell dissemination between the two arms in this study will be undertaken after the randomization of the first 75 patients. If the p-value is < 0.005, the study will be terminated and it will be concluded that the anterior approach technique significantly reduces intraoperative tumor cell dissemination. If the p-value is > 0.65 the trial will be terminated and it will be concluded that there is no significant difference between the two techniques with regard to intraoperative tumor cell dissemination. For a p-value between 0.005 and 0.65, the study will be continued to the total number of 150 patients. The interim analysis is planned using the O'Brien-Fleming boundary with a provision to stop early in favor of the null hypothesis.

Primary comparison of the proportion of patients with disseminated tumor cells in the blood after liver resection will be carried out by Fisher's exact test.

Secondary endpoints as blood loss and duration time of resection will be evaluated by t-test, and amount of used blood units and complication rates will be evaluated by Fisher's exact test. Survival probabilities will be estimated by Kaplan-Meier method and groups will be compared using the log-rank test. A comparison of survival curves will be only feasible after long term follow-up, currently estimated as at least three years. Prognostic relevance of tumor cell detection in blood and bone marrow will be assessed using proportional hazards regression.

The Cochran's Q test will be performed to correlate PCR results with timing of blood collection.

Tumor cell detection rates in blood versus bone marrow samples will be compared with the Mc Nemar's test.

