### Sample size and statistical consideration

150 patients will be accrued to this study. Patients who underwent R1 resection and patients with an intraoperative blood loss of greater than 2000 cc will be excluded.

The sample size of this trial was calculated with regard to the previous results and data from our study on hematogenous tumor cell dissemination during resection of liver metastasis from colorectal cancer [10] and the study on the use of the anterior approach as a new liver resection technique in patients with hepatocellular carcinoma [12]. For statistical sample size calculation a 1:1 randomization in both treatment groups was assumed.

From the analysis of the previous data we expect to detect a difference of at least 30% in the proportion of intraoperative tumor cell dissemination between the two groups. The incidence of hematogenous tumor cell dissemination in the conventional group is reported to be 50–55% and it will be expected to be 15–20% in the anterior resection groups. To achieve a power of 90% (beta = 0.1) approximately 112 patients have to be recruited (two-sided test, Type I error of 5%). Due to the expectation that about 25% of all the patients will have circulating tumor cells at baseline we have to increase the total number of randomized patients to 150 patients (75 in each arm). With this sample size the study will have adequate power to address the primary objective.

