### Randomisation, stratification and blinding

The study is conducted in a prospective randomized manner. After giving informed consent and inclusion into the study, patients will be randomized in the operating room after surgical exploration just prior to resection by using sealed opaque serial numbered envelopes. These envelopes will be supplied by the Clinical Trials Centre (KSC) of the Department of Surgery, University of Heidelberg. The patients will be randomized 1:1 into each arm of the two different liver resection techniques. As stratification factors, the participating institution and the Fong score will be used [15]. The Fong score predicts the risk of recurrence after surgical resection of colorectal metastases to the liver. Two strata will be used (Fong score 0–2 and 3–5).

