### Current status

At the current time point we have randomized 61 patients in 2 different centers. The duration of the trial is expected to be up to 3 more years. About 2–4 patients can be enrolled per month. The interim analysis will be performed during next year. Evaluation and reporting of the clinical and laboratory results will be done within 3 month of the end of recruitment and closing of the database.

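### Randomisation is stratified by institution and Fong group but the named tests are not: a stratified analysis would be a modest, nearly free efficiency gain, not the repair of an error

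*Protocol article*

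**What the plan says.** On allocation (Protocol article, Randomisation, stratification and blinding): "As stratification factors, the participating institution and the Fong score will be used". The Fong score enters in two groups, 0–2 and 3–5. The same section gives the reason: "The Fong score predicts the risk of recurrence after surgical resection of colorectal metastases to the liver".

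On the primary analysis (Analysis): the comparison of the arms' post-resection detection rates in blood "will be carried out by Fisher's exact test". No stratification or adjustment is mentioned. For survival, curves are estimated by Kaplan-Meier and "groups will be compared using the log-rank test", again without strata. Proportional hazards regression is named only for the prognostic relevance of tumour cell detection, not for comparing the arms.

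On the number of strata (Current status): "we have randomized 61 patients in 2 different centers". Two centres and two Fong groups make four strata so far. The final number of centres is not given.

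**The concern.** Stratified allocation balances the arms within institution and Fong group. If those factors predict the outcome, an unstratified test still counts the between-stratum variation as noise, although the design has removed most of it from the treatment comparison. The test then rejects less often than its nominal level and has less power than a test that uses the strata. Fisher's exact test is also conservative for a separate reason: its p-value can take only a limited set of values. What is at stake is efficiency on the primary endpoint and on disease-free and overall survival. False-positive control is not at risk, because both effects act in the conservative direction.

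**Working it through.** **1. Reproduce the planned power.** Inputs from Sample size and statistical consideration: a difference of at least 30 points (taken as 50% vs 20%), two-sided 5%, 90% power, 1:1 allocation, about 112 evaluable patients, and 25% positive at baseline.

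- Normal approximation, per arm: [1.96·√(2·0.35·0.65) + 1.2816·√(0.5·0.5 + 0.2·0.8)]² / 0.30² = (1.322 + 0.821)² / 0.09 ≈ 51.0, so 52 per arm and 104 in total. With continuity correction the total is 116. The stated 112 lies between.
- Exact enumeration of the two-sided Fisher test at 56 per arm gives power 89.8%.
- 112 / 0.75 = 149.3, rounded to 150.

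The plan is therefore correctly sized for the unstratified test it names.

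**2. Primary endpoint: separate the two sources of conservatism.** The CMH statistic without continuity correction is [Σ(aₖ − n₁ₖmₖ/Nₖ)]² / Σ[n₁ₖn₀ₖmₖ(Nₖ − mₖ) / (Nₖ²(Nₖ − 1))]. In stratum k, aₖ is the number of positives in one arm, n₁ₖ and n₀ₖ are the arm sizes, mₖ is all positives and Nₖ is all patients. Comparing Fisher with Pearson chi-square shows the cost of discreteness. Comparing Pearson with CMH shows the cost of ignoring strata.

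The simulation has 20,000 runs and four equal strata (2 centres × 2 Fong groups). Each factor has the same assumed odds ratio (OR), since the article gives none. Mean rates are 35% in both arms for size and 50% vs 20% for power. Cells show size / power in %.

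Exactly 14 per arm in each stratum:

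| Stratum OR | Fisher | Pearson | CMH |
|---|---|---|---|
| 1 | 3.4 / 89.8 | 5.3 / 92.7 | 5.1 / 92.6 |
| 2 | 2.8 / 90.3 | 4.5 / 93.3 | 5.1 / 93.8 |
| 3 | 2.4 / 90.7 | 3.8 / 93.7 | 5.0 / 94.9 |
| 5 | 1.6 / 92.1 | 2.9 / 94.8 | 4.9 / 96.7 |

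Baseline-positive patients are dropped after randomisation, so exact balance will not hold. Repeating with 150 randomised and a random 25% removed:

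| Stratum OR | Fisher | Pearson | CMH |
|---|---|---|---|
| 1 | 3.9 / 90.9 | 5.2 / 92.7 | 5.0 / 92.5 |
| 2 | 3.6 / 90.3 | 4.6 / 92.2 | 4.8 / 93.4 |
| 3 | 3.4 / 90.6 | 4.3 / 92.3 | 5.2 / 94.6 |
| 5 | 2.6 / 91.0 | 3.5 / 92.9 | 5.1 / 96.7 |

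The simulation error is about 0.2 points: √(0.9·0.1/20,000) = 0.002.

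- No stratum effect: CMH minus Fisher is 92.6 − 89.8 = 2.8 points with exact balance and 92.5 − 90.9 = 1.6 with random loss. None of it comes from the strata.
- Strata alone (CMH minus Pearson): 0.5 and 1.2 points at OR 2 and 3 with exact balance; 1.2 and 2.3 with random loss.
- Strongly prognostic strata (OR 5): the whole gain is 96.7 − 92.1 = 4.6 with exact balance and 96.7 − 91.0 = 5.7 with random loss.
- More and smaller strata reduce the gain. With an assumed six unequal centres × Fong group, random loss and no stratum effect, power is 91.0% for Fisher and 91.8% for CMH.
- Continuity correction removes the gain. With it, CMH power is 89.3% at OR 1 with exact balance.

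**3. Survival: log-rank test.** Everything here is assumed: 152 patients, half in each Fong group, five years of follow-up, exponential hazards averaging 0.25 per year in controls (geometric mean over Fong groups), and a treatment hazard ratio (HR) of 0.6; 4,000 runs.

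| Fong HR | Size %, unstratified vs stratified | Power %, unstratified vs stratified | Gain |
|---|---|---|---|
| 1 | 4.9 vs 5.1 | 71.1 vs 71.1 | 0 |
| 1.5 | 4.5 vs 5.1 | 68.5 vs 69.7 | 1.2 |
| 2 | 4.2 vs 5.3 | 65.0 vs 68.6 | 3.6 |
| 3 | 3.1 vs 5.1 | 58.0 vs 67.7 | 9.7 |

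**The case against.** A reader might infer that ignoring the strata gives away the primary power, or that the trial is underpowered. The documents do not support either reading. The unstratified Fisher test delivers the stated 90% to within rounding, so a stratified test adds a surplus and does not fill a deficit. Most of the Fisher–CMH gap at no or moderate stratum effect is discreteness, and choosing Fisher for guaranteed type I error control is legitimate.

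Nothing in the article shows that Fong score or institution predicts CK 20 detection in blood. Fong is described as predicting recurrence. Samples are processed at each institution, which makes a centre effect possible. However, the Laboratory workup and RT-PCR sections specify a standard protocol, positive controls with the shipped samples, and central, blinded, independently double-read PCR.

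The survival gains depend on assumed hazard ratios. The endpoints are secondary and carry no power claim, and the stated prognostic role of Fong covers recurrence, so extending it to overall survival is an inference. Naming a log-rank test does not exclude strata, and an unseen analysis plan may specify them.

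All of this stands. What remains is that the article fixes the primary test by name without the factors it randomises by, and that using them is cheap.

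**Conclusion.** This is a minor efficiency improvement, not an error. Type I error is not inflated, a positive result would not be undermined, and the sample size calculation holds for the test it names.

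On the primary endpoint, moving from Fisher to an uncorrected CMH test raises true size from about 3–4% to about 5%. With four equal strata it adds about 1.5–3 power points if the strata are not prognostic, and up to about 5–6 if they are strongly so. The upper end needs stratum odds ratios that the article does not support, and the lower end shrinks further if many small centres join.

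The case for using the strata themselves is firmest for disease-free survival, where the article calls the Fong score prognostic: about 1, 4 and 10 points at Fong hazard ratios of 1.5, 2 and 3, conditional on a treatment hazard ratio of 0.6.

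**What to change.** Before the interim analysis, and before anyone sees outcomes by arm:

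- Make the primary test a CMH test without continuity correction, stratified by Fong group (0–2, 3–5) and institution, with a prespecified rule for pooling small centres. Use the same test at the interim and final looks.
- Report the stratum-adjusted risk difference with its 95% confidence interval.
- Keep Fisher's exact test as a sensitivity analysis.
- Stratify the log-rank test by Fong group.

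The cost is analysis wording only, with no new data or patients. There is still time: 61 patients were randomised at the time of writing and the interim follows the first 75. There are two downsides. Sparse strata make the pooling rule necessary, above all at the interim, where 75 × 0.75 ≈ 56 evaluable patients over four strata leave about 7 per arm in each. The primary test is also no longer exact, so its 5% level holds approximately and is not guaranteed.

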**Methods/Design:**

This is a multi-centre prospective randomized controlled, superiority trial to compare two liver resection techniques of liver metastases from colorectal cancer. 150 patients will be included and randomized intraoperatively after surgical exploration just prior to resection. The primary objective is to compare the anterior approach with the conventional liver resection technique with regard to intraoperative haematogenous tumor cell dissemination. As secondary objectives we examine five year survival rates (OS and DFS), blood loss, duration of operation, requirement of blood transfusions, morbidity rate, prognostic relevance of tumor cell detection in blood and bone marrow and the comparison of tumor cell detection by different detection methods.

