**Exclusion criteria**

• Any extrahepatic disease, even if this will be resected concomitantly
• Liver cirrhosis
• Grossly positive lymph nodes in the hepatoduodenal ligament
• Positive margins after liver resection (R1) (Patients will be excluded from further follow up, the patient's data however will be recorded).
• Patients with an intraoperative blood loss of >= 2000 cc will be excluded from the analysis of tumor cell detection in blood samples but will be included in the rest of the analyses.

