### Endpoints

As primary endpoint, we choose the tumor cell detection rate in blood samples obtained intraoperatively using a CK 20 RT-PCR. The method is already established and this was the endpoint for the sample size calculation and further decision making. As secondary endpoints, overall survival and disease-free survival will be recorded during the follow-up in both groups. Further secondary endpoints are blood loss, duration time of resection, number of blood products transfused, prognostic relevance of tumor cell dissemination to the bone marrow, and postoperative complications. All these parameters will be collected prospectively as part of the study protocol.

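### The number of blood products transfused is a count, but the protocol tests it with Fisher's exact test and gives no cut-off; a rank test fits the endpoint better (minor).

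*Protocol article*

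**What the plan says.** The Endpoints section of the protocol article defines the transfusion endpoint as a number per patient: "Further secondary endpoints are blood loss, duration time of resection, number of blood products transfused". The Analysis section names the test: "amount of used blood units and complication rates will be evaluated by Fisher's exact test". It does not say whether the units are to be dichotomised, grouped or left as a full table of counts.

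The abstract (Methods/Design) describes the same item as "requirement of blood transfusions", and the aim of the study uses a similar phrase. That wording could mean any versus none, but neither the Endpoints nor the Analysis section says so.

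For the continuous operative measures the Analysis section states: "Secondary endpoints as blood loss and duration time of resection will be evaluated by t-test". Patients with an intraoperative blood loss of 2000 cc or more "will be excluded from the analysis of tumor cell detection in blood samples but will be included in the rest of the analyses", so they count in the comparison of blood loss.

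**The concern.** Fisher's exact test suits a yes/no outcome such as the occurrence of a complication. The number of units is an ordered count, and there are two ways to apply the test to it.

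- **Full table of counts (the r x c extension).** The values 0, 1, 2, 3 and so on become unordered labels. The test then looks for any difference in pattern, not for more blood used in one arm.
- **Any versus none.** The 2x2 test is valid, but a patient given one unit counts the same as a patient given six, and the endpoint as defined is not analysed. The cut-off is also unstated.

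At stake is a secondary comparison of the two techniques. The trial is not sized for it, so an inefficient test makes it more likely that a real difference in blood use is reported as no difference.

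**Working it through.** **Inputs from the article.** Sample size and statistical consideration: "increase the total number of randomized patients to 150 patients (75 in each arm"), 1:1 allocation, two-sided 5%. Baseline-positive patients are excluded from the primary analysis only, so 75 per arm is taken for transfusion. It is an upper limit, since some patients may be removed for a change of technique.

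**The plan's own figure.** The article gives no power, SD or distribution for transfused units or blood loss; its only calculation is for the primary endpoint. With 50% versus 20% and 56 per arm, the exact power of Fisher's test is 89.8%, against the stated 90% with about 112 patients. Then 112 / (1 − 0.25) = 149.3, rounded to 150. The sample size is therefore reproduced and is not in question.

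**Check 1: zero-inflated counts (assumed), 75 per arm.** The arm with fewer transfused patients also receives fewer units. The count-table and Wilcoxon columns come from 500 simulated trials per row, with the r x c Fisher p-value from 400 permutations; the Monte Carlo standard error is at most √(0.25/500) = 2.2 points. The any/none column is exact: the binomial probabilities of all 2x2 tables with Fisher p ≤ 0.05 are summed.

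| Transfused, arm 1 vs 2 | Fisher, count table | Fisher, any/none | Wilcoxon | Loss, count table | Loss, any/none |
|---|---|---|---|---|---|
| 50% vs 30% | 41.6% | 66.7% | 82.2% | 40.6 | 15.5 |
| 55% vs 32% | 51.6% | 79.0% | 85.4% | 33.8 | 6.4 |
| 60% vs 35% | 70.0% | 85.4% | 96.6% | 26.6 | 11.2 |

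**Check 2: negative binomial counts (assumed), mean halved, 75 per arm.** With mean m and dispersion k, P(no units) = (k/(k+m))^k. For m = 2, k = 1 this is 1/3, so 66.7% are transfused; for m = 1, k = 1 it is 1/2, so 50%. Any/none power is exact. Unordered categories are 0 to 4 and 5+, with a chi-square test standing in for the r x c Fisher test (2,000 simulations). Wilcoxon uses 5,000 simulations.

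| Means, k | Fisher, any/none | Unordered categories | Wilcoxon | Loss, any/none | Loss, unordered |
|---|---|---|---|---|---|
| 2 vs 1, 0.5 | 32.7% | 41.2% | 53.5% | 20.8 | 12.3 |
| 2 vs 1, 1 | 50.2% | 61.8% | 79.9% | 29.7 | 18.1 |
| 1.5 vs 0.75, 0.5 | 33.6% | 36.4% | 53.2% | 19.6 | 16.8 |
| 3 vs 1.5, 1 | 43.2% | 69.1% | 84.5% | 41.3 | 15.4 |
| 1.5 vs 0.75, 0.3 | 20.9% | 23.1% | 34.4% | 13.5 | 11.3 |

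With equal arms (mean 2, k = 0.5) the rejection rates are 4.0% for Fisher any/none, 5.2% for unordered categories and 5.0% for Wilcoxon. The issue is efficiency, not validity.

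**Check 3: blood loss, assumed log-normal, 25% lower in one arm, 75 per arm (4,000 simulations).**

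| SD of log volume | t-test | Wilcoxon | Difference |
|---|---|---|---|
| 0.5 | 90.9% | 92.7% | 1.8 |
| 0.7 | 60.3% | 68.1% | 7.8 |
| 1.0 | 27.7% | 37.9% | 10.2 |

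With no true difference, the t-test rejects in 4.5% to 5.4% of trials. Its error rate holds even under strong skew.

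**The case against.** **The plan may mean any versus none.** Units share a clause with complication rates, and the abstract and aim speak of transfusion requirement. On that reading the test is valid and, in Check 1, the loss falls from 27–41 points to 6–16. This stands as a limit on size, but it does not remove the point: Endpoints and Analysis both name a quantity, and Check 2 shows any/none losing up to 41 points. All scenarios let the number of units fall together with the share transfused. If the arms differed only in that share, any/none would lose less.

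**The article is condensed.** A cut-off may stand in the full study protocol. That is fair for the cut-off. The choice of test, however, is stated in the article, and it does not match the endpoint stated there.

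**Two stronger inferences a reader might draw.** The first is that the t-test for blood loss is also wrong. The documents do not support this. They give no SD or distribution, and the 2000 cc rule shows only that such losses were provided for, not how often they are expected. A t-test keeps the ordering, its type I error holds in Check 3, and mean volume is a legitimate quantity to compare. The second is that these are the trial's main safety evidence. The article calls them secondary endpoints, and it also records postoperative complications and adverse events.

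**Conclusion.** The concern holds for transfused units only. The endpoint is a count, and Fisher's exact test either ignores its order or discards the number of units. The loss against a rank test is about 6 to 40 points of power at 75 per arm. Every figure in that range rests on assumed count distributions, because the documents give none; the direction was the same in all eight scenarios tried. Fisher's test is appropriate for complication rates, and the t-test for blood loss can stay. The primary endpoint, sample size and interim rules are unaffected. Severity: minor.

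**What to change.** In the Analysis section, state that the number of units transfused is compared with the Wilcoxon rank-sum test, optionally in its van Elteren form stratified by centre and Fong group (0–2, 3–5), the two randomisation factors. Keep Fisher's exact test for any transfusion (yes/no), named as such, and for complication rates. Optionally, add a log-scale or rank analysis of blood loss as a sensitivity analysis beside the t-test.

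The cost is one or two sentences. If units are recorded per patient, as the endpoint implies, no new data are needed. The article reports 61 patients randomised and the interim analysis still ahead, so at that stage the change could be made before any planned comparison.
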